# Outcomes

All outcomes are measured over time from baseline to 12 weeks.

## Primary outcome

- Knee-heel length (mm)
- Length/height velocity(cm)

## Secondary outcomes

- MUAC (mm)
- Height-for-age z-scores (HAZ)
- Weight-for-height z-scores (WHZ)
- Weight-for-age z-scores (WAZ)
- Child development index (CDI)
- Head circumference over time
- Weight gain (g)
- Haemoglobin (Hb)
- Body composition
- Bioimpedance: FM (kg), FFM (kg), FMI (kg/m^2^), FFMI (kg/m^2^)
- Skin folds: triceps, subscapularis mm/week

## Tertiary outcomes

Blood hormone markers

- Insulin-like Growth Factor-1 (IGF-1)
- Insulin

Blood markers of systemic inflammation

- C-reactive protein (CRP)
- Alpha-1-acid glycoprotein (AGP)

Blood markers of enteric function

- Citrulline.
- Blood markers of micronutrients status Iron (ferritin and soluble transferrin receptor)
- Vitamin B12
- Folate
- Vitamin A (retinol binding protein)
- Stool markers of intestinal inflammation Myeloperoxidase (MPO)
- Neopterin (NEO)
- Alpha-1-antitrypsin (AAT)

Gut microbiota

Safety, morbidity and loss to follow-up

- Proportion deteriorated to MAM, measured as WHZ ≤ -2 and >-3 or MUAC ≤ 125 and >115mm) and proportion deteriorated to SAM, measured as WHZ <-3, MUAC <115mm or presence of nutritional oedema.
- Proportion of participants who die during the study period (mortality)
- Number of morbidity episodes, duration and severity (diarrhea, pneumonia, fever, malaria, other) during the intervention period
- Proportion lost to follow-up during the study period

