### Exclusion criteria

- SAM; measured as MUAC < 115mm OR weight-for-height z-score < -3 OR bilateral pitting oedema
- Medical complications requiring hospitalization.
- Obvious disability that impedes eating capacity.
- Disability that makes length/height assessment problematic
- Participation in another study or program which impacts on this study or previously enrolled in this study.
- Family plans to move away from the catchment area in the next 6 months.
- History or known allergy to peanuts or milk.

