# Deterioration and referral

Children identified as having SAM (MUAC < 115 mm OR WHZ <-3 OR bipedal pitting oedema) prior to inclusion, or participants in the study who deteriorate to SAM (without other complications) are referred for outpatient treatment of SAM (OTC). If the child also has complications, they are referred to inpatient care (ITC). Those identified as having MAM but who are younger than the recruitment age, will be referred to local NGO services or other health facilities for caregiver nutritional/social support (where available). All participants requiring hospital attention will be referred for treatment and attempts will still be made to follow-up on the child wherever possible.

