# Concomitant care for study participants

Participants will not be provided with any medical treatment by the study. Wherever treatment is needed, children are referred for the necessary medical attention.

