## Clinical examination

A thorough physical examination is carried out at baseline including rapid tests for HIV and Malaria and assessment for vital signs (pulse, blood pressure and respiratory rate). At follow-up clinic visits thereafter, a short clinical review is conducted including information on recent medical history and milk consumption. If an illness is suspected, a treatment is recommended but not provided by the study. If necessary, the child is referred for treatment. Where relevant, the resolution/worsening of adverse events is monitored by clinic staff. The SOPs describe the process in further detail.

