## Anthropometrics

Anthropometrics will be taken in repeated measures and on the left side of the body wherever possible. To reduce variation in the measurements, in as much as is possible, the same study staff will take anthropometric measurements, each having been specifically trained in anthropometrics. All equipment is calibrated regularly and the same equipment used (wherever possible) between study sites. All anthropometric measurements are feasible in the study context and are not invasive or harmful to participants.

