## Deterioration and loss to follow-up

*Proportion deteriorated to MAM or SAM* is the proportion of children who have deteriorated according to their status at inclusion. Either to MAM, measured as MUAC < 125 mm and ≥115mm or WHZ between -3 and -2, OR the proportion of children who have deteriorated to SAM, measured as WHZ <-3, MUAC <115mm or the presence of nutritional oedema.

*Proportion and qualification of morbidity* is the number of episodes, number of days with and the qualification of morbidity, during the 12 week intervention period. During the baseline clinical examination, signs and symptoms of the following are assessed: pneumonia (moderate or severe), diarrhea [acute watery (<14 days), acute bloody (<14 days), persistent (≥14 days)], fever (>38⁰C), common cold and other. The caregiver is given an exercise book at inclusion to be used to record morbidity information if the child visits another clinic or is admitted. If the caregiver brings this book to the clinic visit, it can be used to inform the clinician. In addition, caregiver perceived morbidity is assessed (when possible) with phone call follow-up over the 12 week intervention period.

*Mortality* is the proportion of participant deaths recorded during the 12 week intervention period.

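### Deterioration to MAM, a tertiary safety outcome, has conflicting cut-offs in two protocol sections, and one of them leaves MUAC 115 mm and WHZ -3 outside both MAM and SAM

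*Protocol*

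**What the plan says.** Protocol section 17 (Tertiary outcomes) lists this outcome with the safety and morbidity outcomes: "Proportion deteriorated to MAM, measured as WHZ ≤ -2 and >-3 or MUAC ≤ 125 and >115mm".

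Protocol section 22 (Deterioration and loss to follow-up) defines the same outcome again. The proportion "is the proportion of children who have deteriorated according to their status at inclusion", with the class given as: "Either to MAM, measured as MUAC < 125 mm and ≥115mm or WHZ between -3 and -2".

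Both sections define SAM identically, as WHZ below -3, MUAC below 115 mm, or nutritional oedema. The same strict cut-offs appear in the protocol summary, in section 14 (Deterioration and referral) and in section 11 (Exclusion criteria): "SAM; measured as MUAC < 115mm OR weight-for-height z-score < -3 OR bilateral pitting oedema".

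The abbreviations and definitions pages do not define MAM, and nothing states which of the two sections governs.

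**The concern.** The two sections cannot both be followed. Their MUAC bands include and exclude opposite ends, so a child measured at 115 mm or at 125 mm is classed differently depending on which section is programmed. Section 17 gives explicit WHZ endpoints; section 22 does not say whether -3 and -2 belong to the band.

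Section 17 also has a fault of its own. Its MAM band starts above 115 mm and above -3, while its SAM band ends below 115 mm and below -3. The bands do not meet, and the gap lies at the severe edge of MAM. Take a child whose WHZ stays above -2 and whose MUAC falls from 130 mm at inclusion. At a visit where MUAC reads 120 mm the child is MAM, but at a visit where it reads 115 mm the child is in no class, although that is the worse value. At stake is one reported safety proportion, which has two possible answers and an undefined point where MAM should join SAM.

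**Working it through.** The protocol states no figure that depends on these definitions, so there is none to reproduce. The check applies both rules to the boundary values.

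**Rules as written**

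- Section 17, MAM: 115 < MUAC ≤ 125 mm, or -3 < WHZ ≤ -2.
- Section 22, MAM: 115 ≤ MUAC < 125 mm, or WHZ between -3 and -2 (ends not stated).
- Both sections, SAM: MUAC < 115 mm, or WHZ < -3, or oedema.

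**Step 1. MUAC alone (WHZ above -2, no oedema)**

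| MUAC, mm | Section 17 | Section 22 |
| --- | --- | --- |
| 114 | SAM | SAM |
| 115 | neither | MAM |
| 116 to 124 | MAM | MAM |
| 125 | MAM | neither |
| 126 | neither | neither |

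**Step 2. WHZ alone (MUAC above 125 mm, no oedema)**

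| WHZ | Section 17 | Section 22 |
| --- | --- | --- |
| -3.01 | SAM | SAM |
| exactly -3 | neither | MAM if the ends count, otherwise neither |
| -2.99 | MAM | MAM |
| exactly -2 | MAM | MAM if the ends count, otherwise neither |

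**Step 3. Both criteria together.** The gap in section 17 applies to each criterion separately, and the other criterion can close it. MUAC 115 mm with WHZ -2.5 is MAM in both sections, through WHZ. WHZ -3 with MUAC 120 mm is MAM in both, through MUAC. MUAC 115 mm together with WHZ -3 is neither in section 17 and MAM in section 22.

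**Step 4. Can such children be in the trial?** Yes. Section 11 excludes only MUAC below 115 mm, WHZ below -3, or oedema, so a child at exactly 115 mm or exactly -3 is eligible. The same values can also occur at any follow-up visit.

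**Step 5. Size.** The protocol gives no MUAC distribution, no expected change in MUAC and no recording precision, so the number of children affected cannot be computed. Only recordable values can be counted, and that needs an assumed precision:

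- Whole millimetres: 125 - 115 + 1 = 11 values, of which 2 differ (2/11 = 18%).
- Tenths of a millimetre, for example if readings are averaged: (125 - 115)/0.1 + 1 = 101 values, of which 2 differ (2/101 = 2%).

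These are shares of values, not of children. Section 22 (Anthropometrics) says "Anthropometrics will be taken in repeated measures" but not whether readings are averaged, so either precision is possible.

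**The case against.** The strongest case against acting is that this is boundary wording in one tertiary outcome. Whichever definition is chosen would apply to all five groups, and nothing suggests that it would favour one of them. MUAC and WHZ are also secondary outcomes in their own right, and those are unaffected. The data safety monitoring board receives fatalities, serious adverse events and reasons for termination, and its one stopping rule is on mortality. All of this stands, and it limits the severity.

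It can also be said that section 25 promises a statistical analysis plan before unblinding, which could settle the matter. That carries less weight. The protocol did not leave the cut-offs open; it fixed them twice, incompatibly, so an analysis plan would have to overrule one section. How to class a child who meets MAM on one criterion and SAM on the other is different: that is a derivation rule properly left to the analysis plan, and it is not raised as a fault here.

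A reader might infer that a child improving from 115 to 116 mm would be counted as having deteriorated. The documents do not support this. It needs section 17's bands combined with section 22's comparison against inclusion status, a hybrid that neither section states. Under section 22's own band that child is MAM at both times, and a rising MUAC is not deterioration in the ordinary sense.

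A reader might also infer that enrolled children with MAM have no route to care, because section 14 says "Those identified as having MAM but who are younger than the recruitment age, will be referred to local NGO services or other health facilities" and names no such referral for participants. That sentence concerns children too young to enrol. For participants, section 15 says "Wherever treatment is needed, children are referred for the necessary medical attention", and section 22 (Clinical examination) says "If necessary, the child is referred for treatment". A MAM rule for the reference group alone would also require clinical staff to know who is in that group, which section 20 (Blinding) rules out.

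**Conclusion.** The inconsistency is real and follows from the text alone. The two sections class MUAC 115 mm and 125 mm in opposite ways. Section 22 leaves the WHZ endpoints open. Section 17 leaves a MUAC of exactly 115 mm (with WHZ above -2), or a WHZ of exactly -3 (with MUAC above 125 mm), in neither MAM nor SAM. Nothing else in the protocol resolves it.

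Severity is minor. Only exact boundary values of one tertiary safety outcome are affected. The MUAC values matter most if readings are kept in whole millimetres, which is an assumption. It would go too far to infer that a sizeable number of children are misclassified, or that safety oversight is weakened. The protocol gives no data from which to count children, and the SAM cut-offs that govern exclusion and referral agree throughout. The mortality stopping rule, the sample size and the primary outcomes do not use the MAM definition.

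**What to change.** Use one definition of MAM in sections 17 and 22, contiguous with SAM: MUAC at least 115 mm and below 125 mm, or WHZ at least -3 and below -2, in a child who does not meet SAM (including by oedema). Apply it both to status at inclusion and at each follow-up visit.

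Section 22's MUAC band already has this form, so the edit is to align section 17 with it and to state the WHZ endpoints in both places. With SAM strictly below 115 mm and below -3, the two classes then meet with no gap. The change needs no new measurement, visit or participant, and leaves eligibility, care and blinding as they are. The cost is the wording change, which should be made before the outcome is analysed.

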## Other assessments

Additional information collected at baseline:

- Demographics, medical history
- Physical examination
- Dietary intake assessment
- WASH assessment taken at initial home visit
- Intermittent follow-up on child health status and compliance throughout study

# Sample size

The sample size calculation is generic, based on the ability to detect differences in terms of standard deviations. Conservatively, we want to be able to detect a 0.35 SD or greater difference between any two groups with 5% significance and 80% power. For this, we need 129 children in each group, but to allow for 10% loss to follow-up, we will include 150 children in each group. However, given the factorial design, if there are no interactions between the two experimental interventions, we will be able to compare two groups of 300 children each, which will enable us to detect a difference as small as 0.24 SD. In the Treatfood trial, the SD of knee‐heel length at baseline was 18.1 mm [17]. Hence, a 0.24 SD difference corresponds to 4.3 mm. In secondary analysis, we will compare the 600 supplemented children with 150 unsupplemented. These group sizes will allow us to detect a 0.27 SD difference, corresponding to 4.9 mm.

# Schedule of measurements and assessment

**
[figure not shown]
**

**
[figure not shown]
Figure 4: MAGMAM data collection time-points and visits.**

Timeline for enrolment, interventions, assessments and visits for each participant enrolled in the study. Phone follow-up and home visits are unfixed time points depending on need and availability. Time points are considered valid if taken within ±7 days of baseline, week 2 and week 4 and ±14 days from all other time points.

# Assignment of interventions

## Stratified block randomisation

Site-stratified, block-randomisation will be used to allocate children to the four intervention groups and the reference group. Each site will have a separate randomization list. This ensures that the numbers receiving each supplement or no supplementation will be closely balanced between groups and at each of the study sites. In order to maintain the unpredictability of the random sequences, large and randomly varied block sizes will be used.

## Allocation sequence generation

The allocation sequence will be computer generated using [www.randomization.com](http://www.randomization.com) or a similarly appropriate computer randomisation system, prior to study start. The sequence will be generated by a member of staff at the University of Copenhagen in Denmark, who is external to implementation of the study.

## Allocation sequence concealment

The allocation sequence is not accessible to study personnel besides the product distribution staff. They are able to see the product code for treatment assignment but are unable to make any changes to allocation and will not have access to the blinding code. A member of staff at the University of Copenhagen, who is external to data collection, will keep a secure copy of the allocation sequence.

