| **Criteria for inclusion:**   - Age 12 - 59 months - HAZ < -2 according to WHO growth standards (2006) - Care-taker able and willing to return for follow-up visits and agrees to phone follow-up - Living within the catchment area - Written informed consent given by parent/caregiver   **Criteria for exclusion:**   - SAM, defined as MUAC <115 mm OR WHZ<-3 OR bipedal pitting oedema - Medical complications requiring hospitalization. - Obvious disability that impedes eating capacity - Disability that makes length/height assessment problematic - Participation in another study which impacts on this study or previous enrollment in this study. - Family plans to move away from the catchment area in the next 6 months. - History or known allergy to peanuts or milk | |
| **Intervention:**  A supplementary food intervention. Of the 750 children included in the study, 600 are randomly allocated to one of four LNS-LQ upon inclusion and 150 are randomly allocated to no supplementation. All children receive nutrition counselling at inclusion. Those randomised to LNS are given one sachet of 100g per day in addition to the home based diet. Each 100g LNS-LQ sachet provides approximately 530kcal, provides up to half of the average daily energy requirements, and satisfies most of the estimated daily micronutrient requirements (age dependent). | |
| **Duration of intervention:**  12 week intervention. | |
| **Data collection and follow-up**  **[figure not shown]** | |
| **Figure 2:** Study design framework and time-points for data collection.  The 750 children with a HAZ <-2 are included and randomly allocated to one of four LNS-LQ or to a reference group. Supplemented children are provided one LNS-LQ sachet per day (in two-week allocations) over a period of 12 weeks. After inclusion, all children, irrespective of allocation are followed-up every 2-4 weeks until 12 weeks. | **[figure not shown]** |
| **Statistical Methods:**  Primary, secondary, and tertiary endpoints are analysed by means of longitudinal data analysis since repeated measurements are recorded per patient. | |

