### Random allocation

Thereafter, caregivers are informed of allocation to supplementation or the reference group. Those not allocated to supplementation are given a token of appreciation (given at each follow-up clinic visit), valued at around 5000 UGX but not more than 10 000UGX, for example clothes soap. If allocated to LNS caregivers are given training concerning appropriate use of LNS before they are allocated a two week supply. Prior to departure all caregivers are given a follow-up plan. Refer to the SOP for further details.

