# Data management

## Data entry

All participant data are collected on a paper case report form (CRF) and are double entered using Epidata software (<https://www.epidata.dk/>). The secure electronic data collection platform REDCap (Open Source Vanderbelt University) may be used for specific tasks such as participant registration and randomisation. However, these processes can be carried out without REDCap should an internet connection be unavailable. Data should be primarily entered into the CRF and not written down elsewhere unless stipulated in the SOP.. All study staff are trained extensively in how to fill in the sections of the CRF that are relevant to their role. Selected senior staff members are responsible for ensuring that data entry is complete.

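### Product distribution staff at each site have access to the pre-generated allocation list, with no stated limit to children already enrolled, so concealment of the reference arm rests on separation of roles alone

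*Protocol*

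**What the plan says.** Four parts of the Protocol bear on who can see an assignment, and when.

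- **Section 20, Allocation sequence concealment.** "The allocation sequence is not accessible to study personnel besides the product distribution staff". Of these staff it adds: "They are able to see the product code for treatment assignment but are unable to make any changes to allocation". They do not hold the blinding code. A member of staff in Copenhagen outside data collection keeps a secure copy.
- **Section 20, Allocation sequence generation and Stratified block randomisation.** The sequence comes from a named website "or a similarly appropriate computer randomisation system, prior to study start". "Each site will have a separate randomization list", covering the four supplement groups and the reference group, and "large and randomly varied block sizes will be used".
- **Section 20, Blinding, Product codes and Product distribution.** The four supplements carry eight codes whose key is sealed. Reference families know that they receive no product, while clinical staff are not to be told the group. Distributors work at each site, in a separate place, and take no part in clinic data collection.
- **Section 24, Data entry.** REDCap "may be used for specific tasks such as participant registration and randomisation", but these steps may be done without it when there is no internet connection. The fallback is not described.

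**The concern.** Allocation concealment means that nobody able to influence which child enters next can know what that child will receive. Here the one exception to the bar on access is made for people at the site, and what they may access is the sequence rather than a single assignment. Because the list exists in full before the first child is enrolled, access to it would ordinarily include assignments not yet used.

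The reference arm is the weak spot because it has no product and so no code to hide behind. The two outcomes also differ in value to a family. One brings a daily sachet for 12 weeks, with extra sachets where there are other young children in the household. The other brings a token worth at most 10,000 UGX. Village health teams bring children forward, so the order of presentation could be influenced without altering any entry on the list.

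At stake is the comparison of supplemented with unsupplemented children, which is the trial's only randomised evidence on supplementation as such. If children were selected at entry on features that are not measured, the analysis could not reliably repair it.

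**Working it through.** The point is procedural, so the main check sets the provisions side by side and asks what each one protects against.

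| Provision (Protocol section) | Protects against | Hides supplement v no supplement from the list-holder? |
|---|---|---|
| Large, randomly varied blocks (20) | Guessing the next slot from past ones | No: a list that can be read need not be guessed |
| Distributors cannot change allocation (20) | Tampering with an assignment | No: it does not limit knowledge |
| Eight codes, sealed key, no blinding code (20) | Knowing which supplement | No: a reference slot has no product |
| Separate place and role for distributors (20) | Passing information to clinic staff | No: it limits the spread, not the knowledge |
| Other study personnel denied the list (20) | Direct foreknowledge among those who screen and enrol | No: distributors are the exception |
| REDCap (24) | Could enforce release one at a time | Only if used and so configured; it is optional |

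No row says that a distributor sees an assignment only after the child is irrevocably enrolled. For supplement against no supplement, what remains is the separation of people and places.

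**Which comparison is exposed.** The codes leave the 2×2 contrasts among supplemented children largely protected. The exposed contrast is 600 v 150, which section 18 labels secondary. The plan's detectable difference for it reproduces after 10% loss, with 540 v 135 children:

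(1.960 + 0.842) × √(1/540 + 1/135) = 0.270 SD

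The plan states 0.27 SD, and 0.27 × 18.1 mm = 4.9 mm, as stated.

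**Can the bias be sized?** If a fraction *f* of the reference arm were selected children whose prognosis differed by *d* SD, the contrast would shift by *f* × *d*. The Protocol gives neither quantity. Taking purely as assumptions *f* from 5% to 20% and *d* from 0.25 to 1.0 SD:

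- lowest: 0.05 × 0.25 = 0.0125 SD
- highest: 0.20 × 1.0 = 0.20 SD

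The two ends differ sixteenfold (0.20 / 0.0125 = 16), entirely because of the chosen inputs. The formula also assumes that the difference carries fully into the outcome. Outcomes are followed from baseline and analysed longitudinally, so part of a pure baseline difference may not carry through. No single figure is defensible.

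**The case against.** The best defence is that the sentence about product codes describes a read-only view of the code for a child already assigned, so that distributors never see upcoming slots. The Protocol does not say outright that they do. That inference is natural, because access is granted to a sequence that already exists, but it remains an inference. What does not stand is the idea that this second sentence withdraws the access given in the first.

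A reader might go further and infer that allocation is not concealed at the site. The document does not support that. All other study personnel are denied the sequence, which covers the clinical staff who assess eligibility and those who obtain consent. Distributors are kept apart from them. Steering would require a distributor to pass information across that separation, which the Protocol does not set up.

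A reader might also see a contradiction over timing, since the summary says "600 are randomly allocated to one of four LNS-LQ upon inclusion" and the study flow, after baseline measurements and counselling, says "Thereafter, caregivers are informed of allocation to supplementation or the reference group". These are compatible. The second states when caregivers are told, which can follow the allocation itself. Under both, eligibility and consent come first.

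Finally, a randomisation and blinding procedure is listed among the SOPs in section 23 and may specify stepwise release. That is possible and cannot be checked here. It would not remove the need to correct a Protocol sentence that gives wider access.

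**Conclusion.** The point holds in a limited form. The Protocol gives on-site distributors access to the site's pre-generated sequence and nowhere confines them to children already enrolled. Concealment of the reference arm therefore rests on separation of roles, without a technical or physical barrier.

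The primary milk protein and whey permeate contrasts are largely protected by the sealed codes. The secondary 600 v 150 comparison would be open to selection at entry if information leaked. This conclusion rests on reading access to the sequence as including unused assignments. That a motive exists is plausible from the difference between the arms, but the Protocol does not document one.

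It would be tempting to express the risk as a share of the 0.27 SD detectable difference. The document gives neither the fraction of children affected nor how far they would differ, so any such share would only restate the assumptions behind it. The case for acting is that the gap is real and cheap to close, not that a bias of known size is expected.

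**What to change.** Amend the concealment text in section 20 to state that:

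1. Nobody at a site holds the allocation list. The external Copenhagen staff member loads it into the randomisation system.
2. Each assignment is released singly, only after consent and registration have been recorded, and preferably after baseline measurements as well.
3. Release is through the REDCap randomisation already foreseen in section 24. When offline, it is through sequentially numbered, opaque, sealed envelopes opened in order.
4. Distributors see only the codes of children already assigned, which is what they need for restocking.

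Section 24 should name the same fallback, so that randomising without REDCap does not reopen the list.

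The cost is set-up work in REDCap, one set of backup envelopes per site, and a short wait at the clinic when the connection is down. Sample size, visits and analysis are unaffected.
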